#### Primary analysis

The primary effectiveness analysis is the 12-week noninferiority of the within-subject difference between tonic and burst stimulation for the mean daily overall VAS score calculated from the diary. The primary analysis will be conducted using the intention-to-treat population to include data recorded at the 12- and 24-week visits for all randomized participants, except as noted below. Missing data will be imputed using the hot-deck or last-observation-carried-forward method, as appropriate. If participants increase their pain medications during the first 24 weeks of the study, assessment of the effect of the therapy mode on pain will be confounded by the influence of additional pain medications. Thus, participants who increase pain medication (other than acetaminophen) after randomization will be considered treatment failures for the interval during which the increase occurred, and that participant’s baseline mean daily VAS score will be used for that interval in the analysis. A Z-statistic compared with the standard normal distribution will test the null hypothesis that the within-subject difference for the mean overall VAS score is less than or equal to 7.5 mm.

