#### Sample size

Noninferiority of the VAS score during burst compared with tonic stimulation was assumed to be within a window of 7.5 mm on the 100-mm VAS. Based on earlier reports, the standard deviation of the difference between tonic and burst stimulation VAS scores was assumed to be 18.4 mm. With a type I error rate of 0.05, a minimum sample of 76 participants was required to achieve 80% power to show noninferiority between the two stimulation modes.

Previous studies indicate that approximately 29% of subjects trialed with tonic stimulation do not receive a permanent implant and an additional 20% of subjects may be lost to attrition by the 6-month visit [18]. Screen failure rates were originally estimated to be at 15%, but after the first 6 months of enrollment the screen failure rate was amended to 22%. Total enrollment communicated with the regulatory bodies was 173 to account for screen failures, trial evaluation failures, and normal attrition [76/.71 = 108/.80 = 135/.78 = 173 (rounding up at each step)].

The noninferiority margin was set to preserve at least 50% of the expected effect [19, 20]. Assuming, based upon enrollment criteria and past literature [21], the average baseline pain is approximately 75 mm, a 30% improvement in VAS score would be 23 mm. The 7.5-mm margin on the VAS scale would preserve approximately 77% of the effect and would, therefore, be an appropriate margin.

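### The primary crossover analysis permits last-observation-carried-forward without confining it to one waveform period, so some burst–tonic differences can be set to exactly zero

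*Protocol article*

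**What the plan says.** The Primary analysis section bases the endpoint on the mean daily overall VAS score from the diary, "using the intention-to-treat population to include data recorded at the 12- and 24-week visits for all randomized participants". On incomplete data it says: "Missing data will be imputed using the hot-deck or last-observation-carried-forward method, as appropriate". It does not say which of the two methods applies when, or that a carried value must come from the same waveform. The test is introduced as "A Z-statistic compared with the standard normal distribution will test the null hypothesis that the within-subject difference" in mean overall VAS, judged against 7.5 mm.

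The Sample size section sets the margin: "Noninferiority of the VAS score during burst compared with tonic stimulation was assumed to be within a window of 7.5 mm on the 100-mm VAS". The planning SD of the within-subject difference is 18.4 mm. The resulting requirement is worded this way: "With a type I error rate of 0.05, a minimum sample of 76 participants was required to achieve 80% power". On losses, the section expects that "an additional 20% of subjects may be lost to attrition by the 6-month visit".

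Three other places bear on the point. Trial design puts diary assessments at weeks 6 and 12 in the first period and weeks 18 and 24 in the second. The Pain subsection of Assessment tools refers missing diary entries after randomization to the statistical section. Additional analyses promises conservative imputation for missing data and withdrawal, but only for those additional analyses.

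**The concern.** In a parallel-group trial, a carried-forward value at least belongs to the treatment being assessed. In this crossover, week 12 and week 24 are the two sides of the comparison. Carrying a score over the week-12 switch enters the same number on both sides, so the participant adds a difference of exactly 0 whatever the missing waveform would have done.

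Noninferiority is judged at the margin. If burst is really 7.5 mm worse, each forced zero moves the mean toward the claim and also reduces the SD, so both parts of the Z-statistic shift the same way. Single imputation by either named method also treats filled-in values as observed, which understates the standard error; that part is not quantified here.

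The primary analysis does guard against one kind of failure. A participant who increases pain medication is scored at baseline for that interval. Withdrawal without such an increase has no comparable safeguard in the primary test.

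**Working it through.** **Inputs.** From Sample size: margin 7.5 mm, SD of the difference 18.4 mm, type I error 0.05 (side not stated), 76 participants, 20% attrition. Number randomized: 76/0.80 = 95. The share *f* of randomized participants whose difference becomes zero is not in the document. It is an assumption, ranged from 0 to 20%. Differences are burst minus tonic, so positive means burst is worse.

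**The plan's own figure.** For a paired comparison at one-sided 0.05 and 80% power, (18.4 × (1.645 + 0.842)/7.5)² = 37.2, so 38 pairs. The stated 76 equals 2 × 38, and it is also the per-arm size from a two-sample *t* calculation at one-sided 0.05. One-sided 0.025 gives 48 pairs or 96 per arm, neither of which leads to 76. So 76 is reproduced at one-sided 0.05, the main case below; 0.025 is shown alongside.

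**Which losses give a zero.** If carrying is unrestricted and uses the latest available diary:

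| Last diary | Week-12 value | Week-24 value | Difference |
|---|---|---|---|
| Week 6 | week 6, same waveform | week 6, other waveform | 0 |
| Week 12 | observed | week 12, other waveform | 0 |
| Week 18 | observed | week 18, same waveform | not forced |

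**Effect on the test.** With true difference μ and SD σ:

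- mean = (1 − f)μ
- variance = (1 − f)(σ² + μ²) − [(1 − f)μ]²

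At μ = 7.5 and f = 0.10:

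- mean 6.75
- variance 0.9 × (338.56 + 56.25) − 45.56 = 309.77, so SD 17.60
- standard error 17.60/√95 = 1.806
- (7.5 − 6.75)/1.806 = 0.415
- false noninferiority about P(Z < 0.415 − 1.645) = P(Z < −1.230) = 10.9%

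At f = 0.20: mean 6.0, SD 16.73, standard error 1.716, and 1.5/1.716 = 0.874, giving P(Z < −0.771) = 22.0%.

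Simulation (40,000 trials per row, N = 95, zeros rounded to whole participants) agrees:

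| f | Mean (mm) | SD (mm) | Error, one-sided 0.05 | Error, one-sided 0.025 |
|---|---|---|---|---|
| 0 | 7.50 | 18.4 | 5.1% | 2.7% |
| 5% | 7.13 | 18.0 | 7.5% | 4.3% |
| 10% | 6.75 | 17.6 | 11.7% | 6.4% |
| 15% | 6.38 | 17.2 | 15.6% | 9.5% |
| 20% | 6.00 | 16.7 | 22.4% | 14.2% |

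A separate run of 20,000 trials gave 7.9%, 11.5%, 15.7% and 22.3% for the last four rows at one-sided 0.05.

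**Other true differences (one-sided 0.05, f from 0 to 20%).**

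- Burst 5 mm worse: the chance of declaring noninferiority goes from 38% to 66%.
- No difference: the mean is unbiased and the pass rate moves only from 99.0% to 99.7%.
- Burst 5 mm better: the observed advantage shrinks from 5 to 4 mm.

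**Without forced zeros.** If data are missing at random, 76 completers give 5.1% (one-sided 0.05) or 2.7% (0.025) error at the margin. Power at no true difference is 97% or 94%.

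**The case against.** The text does not say that a score passes from one waveform to the other. It names two methods and leaves the choice open, and hot-deck does not by its nature produce a zero. Since missing diary entries are referred to the same section, part of the sentence may concern days within one 7-day diary, where carrying stays within a waveform. Week 6 can fill week 12, and week 18 can fill week 24, without crossing over. If the carryover test rejects, only first-period data are used and no forced zero arises. The attrition figure comes from earlier work and is not split by visit, and the Discussion expects the enrichment strategy to keep attrition low. The article also condenses a fuller protocol.

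Most of this stands, and it limits the size of the point. A reader might infer that the plan prescribes cross-waveform copying; the documents show only that it is not excluded. A reader might also infer that every dropout favors burst. That does not follow, because late losses have a same-waveform value and the pull is toward zero rather than toward burst.

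What remains is a method named for the primary test which, applied as worded to someone lost before week 18, can give a wrong difference. The conservative imputation mentioned elsewhere does not reach that test.

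**Conclusion.** The point holds as a missing restriction on a stated primary-analysis rule. Carrying forward is allowed across the crossover. Where that happens, the difference is exactly 0 and the noninferiority test is anti-conservative if burst is truly worse.

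At a true difference of 7.5 mm and one-sided 0.05, the error rises from 5% to about 7.5–8% with 5% zeros and about 11% with 10% zeros. The figure of about 22% is tempting as a headline, but it is a worst case: it needs all 20% attrition to fall before week 18 and all of it to be filled by carrying forward. The document supports neither as an expectation.

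The figures assume 95 randomized, SD 18.4 mm and dropouts who resemble completers. If participants left because burst worked poorly, the bias would be larger, but the document gives no basis for sizing that.

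**What to change.** 1. State that no value may be carried across the week-12 crossover. If carrying forward is kept, allow only week 6 to week 12 and week 18 to week 24, and say when each imputation method applies.
2. Handle a wholly missing period with a likelihood-based mixed model on the diary means at weeks 6, 12, 18 and 24 (waveform, period, sequence, visit, participant), reading the contrast at weeks 12 and 24. Multiple imputation within waveform is the alternative. Either avoids treating imputed values as observed.
3. Add a sensitivity analysis that imputes missing burst values under the noninferiority null (7.5 mm worse), followed by a tipping-point analysis.

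**Cost.** All four diaries are already scheduled, so no new data are needed, and the power figures above show ample room. The change is a short wording amendment and some programming. The study is ongoing, and protocol changes are reported to each site's IRB and to the FDA. The model relies on data being missing at random, which the third step probes.

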**Fig. 2 Fig2:**
[figure not shown]
Standard Protocol Items: Recommendations for Interventional Trials (SPIRIT) figure

At up to 20 centers in the U.S., Institutional Review Board (IRB) approval is obtained (refer to its “Declarations” page), and eligible enrolled participants undergo additional screening and participate in a standard SCS trial evaluation using tonic stimulation. Those with a successful SCS trial evaluation are implanted with the Prodigy™ neurostimulation system (St. Jude Medical, Plano, TX, USA) that can deliver both burst and tonic waveforms. Lead position for the permanent system is determined by placement for optimum paresthesia coverage during the tonic stimulation trial evaluation. After a 2–3 week surgical recovery period, participants with the permanent system are randomized to receive one of the two treatment sequences over the subsequent 24 weeks.

During the control phase, participants use one waveform for 12 weeks then cross over to the other waveform for the remaining 12 weeks. Participants are randomly assigned (1:1) at each study site using computer-generated assignment to receive 12 weeks of tonic stimulation followed by 12 weeks of burst stimulation, or 12 weeks of burst stimulation followed by 12 weeks of tonic stimulation. Participants in both groups complete assessments at 6, 12, 18, and 24 weeks after randomization.

To enhance participant compliance with the study protocol, a washout period was not employed when participants crossed over. This decision was based on previous reports suggesting that 25–80% of patients may fail to comply with the study protocol when asked to undergo periods without stimulation [9, 10]. Assessments occur at a minimum of 6 weeks after changing stimulation modes, which is adequate time to ensure that any after-effects of the previous therapy will not influence the assessment of the current therapy [11, 12].

During the open-label phase of the study, participants attend study visits for assessment every 6 months for up to 2 years post randomization. Perceptible differences in paresthesia between the two waveforms are likely, thus neither patients nor investigators are blinded to treatment sequence.

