#### Pain

A daily Pain Diary is completed for the 7-day period prior to each study visit. In the diary, participants are asked to rate pain intensity using the Visual Analog Scale (VAS), which consists of a horizontal line 100 mm in length, anchored by word descriptors on each end (no pain to worst imaginable pain). Higher scores indicate higher pain levels. Each diary entry includes four different VAS scores to permit calculation of a weekly average for daily overall pain, worst overall pain, trunk pain, and limb pain. Participants arriving at the baseline visit with less than seven diary entries repeat the baseline diary. If repeating the baseline diary results in less than seven entries, the participant is deemed a screening failure. Participants complete the baseline pain diaries without making changes to their current, stable pain medications. After randomization, missing diary entries are accommodated during data analysis (see “Statistical methods” section for more details).

Participants also complete the Short-Form McGill Pain Questionnaire version 2 (SF-MPQ-2), a validated questionnaire that measures the qualities of pain [13]. The SF-MPQ-2 is a self-administered questionnaire consisting of 22 different pain descriptors. The participant indicates the intensity of each pain descriptor as it pertains to the participant’s pain experience. Intensity ratings for each descriptor are provided on a scale ranging from 0 (“none”) to 10 (“worst possible”). The total SF-MPQ-2 score is the sum of the score of three sensory subscales (continuous, intermittent, and predominantly neuropathic pain descriptors) and one affective subscale. Higher scores indicate a higher severity of symptoms.

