### Study visits

Table 2 shows the assessments scheduled for each study visit. At the enrollment visit, participants adhering to the initial inclusion/exclusion criteria sign informed consent, complete assessments, and start the VAS Pain Diary. If required of female participants, a pregnancy test is performed. Participants who meet all the inclusion/exclusion criteria after initial assessments and completion of the baseline Pain Diary complete additional assessments and are scheduled for the tonic stimulation trial evaluation period for 3–7 days. Participants with a successful trial, defined as a patient-reported pain reduction of at least 50%, proceed to a permanent implant. After a surgical recovery period of 2–3 weeks, participants are randomized (1:1 at each site) using an online electronic program provided by St. Jude Medical and the prescribed programming is activated. All participants receive a patient programmer that enables activation of the ON and OFF positions and adjustments to amplitude within the prescribed range.

During the control phase of the study, participants attend follow-up visits at the mid-point and end of each of the two 12-week phases of treatment. At the 12-week visit, participants cross over to the second stimulation mode of their treatment sequence and continue in the study for an additional 12 weeks (through 24 weeks).

Participants are programmed to their preferred stimulation mode at the end of the 24-week visit. Subsequently, participants attend follow-up visits every 6 months for up to 2 years. During this open-label phase, participants can request reprogramming and may use either stimulation mode or both, as needed to maintain adequate therapeutic benefit.

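### The primary analysis permits last-observation-carried-forward without confining it to one stimulation period, so a participant with no diary on the second waveform can be given a difference of exactly 0 mm

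*Protocol article*

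**What the plan says.** All of this is in the Protocol article.

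- **Endpoint** (Primary analysis): "12-week noninferiority of the within-subject difference between tonic and burst stimulation for the mean daily overall VAS score".
- **Population and data** (Primary analysis): "intention-to-treat population to include data recorded at the 12- and 24-week visits for all randomized participants, except as noted below". The exception is a medication increase, for which the baseline score replaces the score of the affected interval.
- **Missing data** (Primary analysis): "Missing data will be imputed using the hot-deck or last-observation-carried-forward method, as appropriate". No rule says which method applies when, or from which visit a value may be carried.
- **Crossover** (Study visits): "At the 12-week visit, participants cross over to the second stimulation mode of their treatment sequence".
- **Diaries** (Trial design, text below Fig. 2): "Participants in both groups complete assessments at 6, 12, 18, and 24 weeks after randomization"; and (Pain): "A daily Pain Diary is completed for the 7-day period prior to each study visit". Each period thus has a mid-period and an end-of-period diary.
- **Attrition** (Sample size): "an additional 20% of subjects may be lost to attrition by the 6-month visit". It is not split by period.

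**The concern.** In a parallel-group trial, carrying a value forward keeps the participant on the same treatment. In this crossover it need not. For someone with a week-12 diary and nothing later, the last observation belongs to the other waveform. Carrying it into week 24 enters a tonic score as a burst score, or the reverse. Someone lost between weeks 6 and 12 could have the week-6 score used for both weeks 12 and 24, with the same result.

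Either way the difference is zero by construction, although the participant gave no information on one of the two modes. In a superiority test such zeros would mostly dilute the effect. In a noninferiority test zero lies on the favourable side of the margin, so a participant with no comparison can count as evidence that the modes are comparable. What is at stake is the type I error of the trial's single primary claim.

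**Working it through.** **Inputs.** From Sample size: margin M = 7.5 mm, SD of the within-subject difference s = 18.4 mm, type I error 0.05 (sidedness not stated), minimum N = 76, attrition 20%. The number randomized is not given; I take n = 76/0.80 = 95. Working down from total enrolment gives nearly the same: 173 × 0.78 × 0.71 = 95.8. I take the difference D as burst minus tonic, positive when burst is worse, with the usual noninferiority null that D is at least 7.5 mm.

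**The plan's own figure.** The paired formula at one-sided 0.05 and 80% power gives (18.4 × (1.645 + 0.842)/7.5)² = 37.2, so 38. Two times 38 is 76, and a two-sample t calculation gives 76 per arm. The stated 76 is thus reproduced in one of these forms, not as a plain paired sample size. Nothing below depends on which form was used, beyond the assumed n.

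**Effect of the zeros.** Let a fraction f have D = 0 by imputation, independently of outcome, and let the rest follow N(7.5, 18.4²), the boundary of the null. Then:

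- mean = 7.5 (1 − f)
- variance = (1 − f) × 18.4² + f (1 − f) × 7.5²
- probability of declaring noninferiority = Φ((7.5 − mean)/√(variance/n) − z), with z = 1.645 or 1.960

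Example, f = 0.10: mean = 6.75; variance = 0.9 × 338.56 + 0.09 × 56.25 = 309.8, so SD = 17.6; standard error = 17.6/√95 = 1.806; Φ(0.75/1.806 − 1.645) = Φ(−1.23) = 0.109.

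| f | about how many of 95 | mean (mm) | SD (mm) | error, one-sided 0.05 | error, one-sided 0.025 |
|---|---|---|---|---|---|
| 0 | 0 | 7.50 | 18.4 | 0.050 | 0.025 |
| 5% | 5 | 7.13 | 18.0 | 0.075 | 0.040 |
| 10% | 10 | 6.75 | 17.6 | 0.109 | 0.061 |
| 15% | 14 | 6.38 | 17.2 | 0.157 | 0.093 |
| 20% | 19 | 6.00 | 16.7 | 0.220 | 0.139 |

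A simulation of 100,000 trials with a fixed count of zeros agrees: 0.078, 0.115 and 0.223 for 5, 10 and 19 zeros at one-sided 0.05. Analysing only those with both periods, with dropout unrelated to outcome, keeps the error at 0.051 to 0.052 (0.027 at one-sided 0.025).

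**Shift of the effective margin.** The expected imputed mean equals 7.5 mm only when the true deficit is 7.5/(1 − f): 7.9 mm at 5%, 8.3 mm at 10% and 9.4 mm at 20%.

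**The case against.** Four stronger readings are tempting, and the article does not support them.

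1. *That the plan requires this imputation.* It does not. Hot-deck is named alongside, the choice is left to judgement, and a full protocol or analysis plan not shown may settle it. The Pain section also sends the reader to the statistical section for missing diary entries, so the sentence may partly concern single missing days within one week, where carrying forward stays on one waveform.
2. *That everyone lost in the second period gets a zero.* A participant who leaves after week 18 has a diary on the second waveform, and that would ordinarily be the value carried. The zero arises for those with no diary in that period. It would extend to all second-period losses only if the phrase "to include data recorded at the 12- and 24-week visits for all randomized participants" were meant to bar week 18 as a source, which the article does not say.
3. *That an error of about 22% is to be expected.* That needs every planned loss to take this form, with none hot-decked, none leaving after week 18 and none leaving before any diary. Intervals with a medication increase are scored at baseline, so they are not carried either.
4. *That zeros always favour noninferiority.* They do so through the mean only when burst is worse. If the modes are equal, the mean is not biased. If burst is better, zeros move the estimate toward the margin. The smaller SD remains in each case.

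These points limit the size of the problem but do not remove it. Including all randomized participants means that whole missed visits must be filled as well as single days, and the quoted sentence is the only rule given for doing so in the primary analysis. The cautious imputations promised under Additional analyses do not govern the primary test. This is also more than omitted detail: the article names a method for the primary test and leaves off the limit that a crossover needs.

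**Conclusion.** The point holds as a permitted bias. Carrying forward is allowed in the primary analysis with no stop at the crossover, and where it is used for a participant with no diary on the second waveform, the difference is 0 mm whatever the true effect.

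At a true deficit equal to the margin, with 95 randomized and one-sided 0.05, the false noninferiority rate goes from 5% to about 7.5% with 5% affected and about 11% with 10% affected; about 22% is the ceiling. This rests on the planning SD, on zeros unrelated to outcome, and on an assumed share affected, because the article does not divide attrition by period or say how it would be imputed. A modest share already matters: 5% is a quarter of the planned attrition and raises the error by half.

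**What to change.** In Primary analysis, state that no value is carried across the week-12 crossover. Week 6 may stand in for week 12, and week 18 for week 24, only within the same period. Where a period has no diary, carry nothing: leave the score missing and estimate the burst-tonic contrast from, for example, a linear mixed model on the week 6, 12, 18 and 24 diaries, with mode, visit and period as fixed effects and participant as a random effect. The model is one suitable choice; the essential change is the stop at the crossover.

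A tipping-point analysis that makes the missing burst scores progressively worse is an optional sensitivity check, and would fit with the cautious imputations already planned under Additional analyses.

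The cost is a change of wording, a little programming and a slightly wider interval, since imputed zeros no longer count as observations. No new data are needed. The change should be fixed before the 24-week analysis is run.

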## Methods

### Objectives

Under an Investigational Device Exemption (IDE), the objective of the study (protocol C-12-07 ver 8.28.14) is to demonstrate safety and efficacy for burst stimulation. As such, the study examines burst stimulation compared to the traditional SCS stimulation mode (tonic stimulation). The primary objective of the study is to establish noninferiority of pain intensity after 3 months of burst compared to 3 months of tonic stimulation. Previous studies [5–8] indicated that burst stimulation was preferred by most subjects even when the magnitude of pain relief was similar. Therefore, the primary objective of noninferiority of pain intensity will establish the therapy as comparable for pain relief to traditional tonic stimulation, and secondary objectives (listed below) will examine the superiority of pain relief and other outcomes that may elucidate the patient experience of burst stimulation.

Secondary objectives are:To demonstrate differences between tonic and burst stimulation in responder rateTo demonstrate significant differences in the presence of paresthesia during tonic stimulation and burst stimulationTo demonstrate that pain relief using burst stimulation is superior to pain relief using tonic stimulationTo demonstrate differences between tonic and burst stimulation adverse eventsTo demonstrate differences between tonic and burst stimulation for quality of lifeTo demonstrate differences between tonic and burst stimulation for worst painTo demonstrate differences between tonic and burst stimulation for function

Additional analyses will examine these objectives after 12 months of therapy.

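### The primary null hypothesis is printed in the wrong direction, so rejecting it cannot show noninferiority

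*Protocol article*

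**What the plan says.** The aim is stated consistently. In Objectives: "The primary objective of the study is to establish noninferiority of pain intensity after 3 months of burst compared to 3 months of tonic stimulation". In Sample size the margin is set: "Noninferiority of the VAS score during burst compared with tonic stimulation was assumed to be within a window of 7.5 mm". The Pain subsection fixes the direction of the scale: "Higher scores indicate higher pain levels".

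The Primary analysis section describes the analysis as "the 12-week noninferiority of the within-subject difference between tonic and burst stimulation for the mean daily overall VAS score". It names the test statistic as "A Z-statistic compared with the standard normal distribution". The hypothesis attached to that statistic is given in these words: it "will test the null hypothesis that the within-subject difference for the mean overall VAS score is less than or equal to 7.5 mm".

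That sentence is the only place in the article where a primary null hypothesis is written. The article gives no alternative hypothesis, no signed contrast and no confidence-limit rule for the primary endpoint. The Additional analyses section makes the superiority test of burst over tonic conditional on noninferiority having been shown.

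**The concern.** In a noninferiority test, the statement to be proved belongs in the alternative. Here it is that burst is worse than tonic by less than 7.5 mm. The null must then be that burst is worse by 7.5 mm or more. The printed null is the region at or below +7.5 mm, so rejection supports a difference above +7.5 mm, which is not what the trial sets out to show.

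The trial is meant to support regulatory approval, and this test decides its primary endpoint and opens the gate to superiority. Taken literally, the rule would either establish inferiority or require superiority by a margin, depending on the order of subtraction. If a non-significant result were taken as noninferiority instead, the chance of wrongly passing an inferior waveform would not be controlled.

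**Working it through.** **Inputs.** From Sample size: margin 7.5 mm; SD of the within-subject difference 18.4 mm ("the standard deviation of the difference between tonic and burst stimulation VAS scores was assumed to be 18.4 mm"); minimum N 76; power 80%; "With a type I error rate of 0.05", with sidedness not stated, so one-sided 0.05 and 0.025 are both shown. Assumed here because the article gives no value: a true difference of 0 mm.

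**The plan's own figure.** The figure of 76 can be reached with a two-group noninferiority formula at one-sided 0.05 and true difference 0, which gives 75 per group by the normal approximation and 76 by the noncentral t. The paired formula gives fewer: [(1.645 + 0.842) × 18.4 / 7.5]² = 37.2, so 38. All of these calculations take burst − tonic ≥ 7.5 mm as the null. The sample size therefore presupposes the opposite direction from the printed hypothesis.

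**What rejection of the printed null would mean.**

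| Reading of the difference | Rejection shows |
|---|---|
| burst − tonic | burst worse by more than 7.5 mm (inferiority) |
| tonic − burst | burst better by more than 7.5 mm (superiority by a margin) |
| absolute difference | the waveforms differ by more than 7.5 mm (non-equivalence) |

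None of the three is noninferiority.

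**Decision thresholds at N = 76.** SE = 18.4 / √76 = 2.11 mm.

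- Printed null: reject if the observed difference exceeds 7.5 + 1.645 × 2.11 = 10.97 mm (one-sided 0.05) or 7.5 + 1.960 × 2.11 = 11.64 mm (0.025).
- Correct null: declare noninferiority if observed burst − tonic is below 7.5 − 1.645 × 2.11 = 4.03 mm (0.05) or 7.5 − 1.960 × 2.11 = 3.36 mm (0.025).

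**Probability of rejection at one-sided 0.05, with the difference taken as burst − tonic.**

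| True difference (mm) | Printed null | Correct null |
|---|---|---|
| 0 | 1.0 × 10⁻⁷ | 97.2% |
| 5 | 0.23% | 32.3% |
| 7.5 | 5.0% | 5.0% |
| 10 | 32.3% | 0.23% |
| 15 | 97.2% | below 0.01% |

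At one-sided 0.025 and a true difference of 0, the two probabilities are 1.8 × 10⁻⁸ and 94.4%.

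**If the difference is tonic − burst.** An 80% chance of rejecting the printed null needs a true advantage of burst of 7.5 + (1.645 + 0.842) × 2.11 = 12.75 mm (13.41 mm at 0.025). Sample size puts a 30% improvement from baseline at 23 mm, so burst would have to beat tonic by more than half of that (12.75 / 23 = 55%).

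**If failure to reject were taken as noninferiority.** The article does not state this rule; it is shown only to close off that reading. With burst − tonic at one-sided 0.05, a waveform truly 7.5 mm worse would pass 1 − 0.05 = 95% of the time, and one truly 10 mm worse would pass 1 − 0.323 = 67.7% of the time.

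**The case against.** The strongest reply is that the intent is plain. The objective, the margin, the sample size, the opening of the Primary analysis paragraph and the conditional superiority test all point to an ordinary noninferiority test. The paragraph names tonic before burst; with tonic − burst, the right null is ≤ −7.5 mm, one minus sign away from what is printed. On this view the sentence is a slip, and the rejection probabilities above describe a test nobody means to run. This is a fair account of how the error probably arose, and it means the point should not be read as evidence that a different analysis is planned. It does not make the sentence correct. A primary decision rule should not depend on the reader to supply a sign, and the article states no other rule to fall back on.

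A second reply is that this is a journal article condensing a fuller protocol, and that the full protocol or SAP may state the hypotheses correctly. They may; they were not available for this review. An order of subtraction left to a fuller document would not by itself be a fault. But the inequality is an affirmative statement, not an omission. If the fuller documents are right, the article conflicts with them and still needs correcting.

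A third point concerns the remedy: asking only for the upper confidence limit to lie below 7.5 mm leaves the threshold open, since it is 4.03 or 3.36 mm depending on the level. That stands, and the fix below names the level.

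**Conclusion.** The concern holds. As printed, the primary null cannot lead to a conclusion of noninferiority under any reading of the difference. The direction is wrong whatever the sample size, SD or significance level; the figures show only how far the printed rule is from the intended one. With SD 18.4 mm, 76 paired participants, one-sided 0.05 and a true difference of 0 mm (our assumption), the printed null would be rejected with probability about 10⁻⁷, against 97.2% for the correct null. It cannot be reconciled with the stated 80% power to show noninferiority. The likely cause is a reversed inequality or a missing minus sign, but because this is the article's only stated primary decision rule and it gates the superiority test, it must be corrected.

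**What to change.** Replace the hypothesis sentence in Primary analysis with wording to this effect:

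> Let D be the within-subject difference, burst minus tonic, in mean daily overall VAS score. The null hypothesis is mean D ≥ 7.5 mm and the alternative is mean D < 7.5 mm. Noninferiority is declared if the upper confidence limit for mean D is below 7.5 mm.

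State the level in the same place and tie it to the type I error in Sample size: the upper limit of a two-sided 90% interval corresponds to one-sided 0.05, and that of a two-sided 95% interval to one-sided 0.025. The general statistical methods text already calls for 95% intervals. On the article's SD and N, with a true difference of 0, the stricter level still gives 94.4% power for the paired test.

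Use the same signed contrast for the superiority test (H0: mean D ≥ 0 against H1: mean D < 0), and say that failure to reject the primary null is not evidence of noninferiority. Check the full protocol and any SAP for the same sentence, and correct it there if it appears.

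The cost is a few lines of text. It changes no participants, visits, data or sample size.
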